## Abstract

**Background:**

Colorectal cancer survivors often experience decline in physical performance and poor quality of life after surgery and during adjuvant therapies. In these patients, preserving skeletal muscle mass and high-quality nourishment are essential to reduce postoperative complications and improve quality of life and cancer-specific survival. Digital therapeutics have emerged as an encouraging tool for cancer survivors. However, to the best of our knowledge, randomized clinical trials applying personalized mobile application and smart bands as a supportive tool to several colorectal patients remain to be conducted, intervening immediately after the surgical treatment.

**Methods:**

This study is a prospective, multi-center, single-blinded, two-armed, randomized controlled trial. The study aims to recruit 324 patients from three hospitals. Patients will be randomly allocated to two groups for one year of rehabilitation, starting immediately after the operation: a digital healthcare system rehabilitation (intervention) group and a conventional education-based rehabilitation (control) group. The primary objective of this protocol is to clarify the effect of digital healthcare system rehabilitation on skeletal muscle mass increment in patients with colorectal cancer. The secondary outcomes would be the improvement in quality of life measured by EORTC QLQ C30 and CR29, enhanced physical fitness level measured by grip strength test, 30-sec chair stand test and 2-min walk test, increased physical activity measured by IPAQ-SF, alleviated pain intensity, decreased severity of the LARS, weight, and fat mass. These measurements will be held on enrollment and at 1, 3, 6 and 12 months thereafter.

**Discussion:**

This study will compare the effect of personalized treatment stage-adjusted digital health interventions on immediate postoperative rehabilitation with that of conventional education-based rehabilitation in patients with colorectal cancer. This will be the first randomized clinical trial performing immediate postoperative rehabilitation in a large number of patients with colorectal cancer with a tailored digital health intervention, modified according to the treatment phase and patient condition. The study will add foundations for the application of comprehensive digital healthcare programs focusing on individuality in postoperative rehabilitation of patients with cancer.

**Trial registration:**

NCT05046756. Registered on 11 May 2021.

**Supplementary Information:**

The online version contains supplementary material available at 10.1186/s12885-023-10728-2.

## Background

Colorectal cancer is the third and second most common cancer worldwide in men and women, respectively [1]. Colorectal cancer survivors often suffer from decline in physical performance and mental health, psychological distress, and difficulty in returning to society after surgery and during adjuvant therapies. For example, 80–90% of individuals who undergo sphincter-preserving surgery experience lower anterior resection syndrome [1, 2]. Patients experience difficulties not only in the active treatment phase but also in expanded phases even after the completion of cancer treatment. Thus, physical fitness, quality of life, and social issues of colorectal patients should be addressed from both immediate and long-term perspectives. To be more specific, clinicians should be aware of the hardships the patients confront according to the characteristics of therapeutic phases and individuality of each patient for comprehensive management of the disease.

Health behaviors, such as physical activity and nutrition, can have positive effects on physical functioning, quality of life, and symptoms related to cancer treatment, such as fatigue among cancer survivors [3]. In fact, low muscle mass is frequently observed in patients with colorectal cancer, ranging between 12 and 60% [4]. It serves as a predictor of postoperative complications, chemotherapy toxicity, reduced quality of life, and decreased overall survival [4]. Previous studies have reported that exercise has the potential to reverse severe muscle loss in patients with cancer [5]. Furthermore, nutritional support such as adequate dietary intake and high protein is reported to contribute to muscle mass preservation [4]. Hence, a multimodal approach including nutritional intervention and fitness programs is essential in patients with colorectal cancer.

At present, many cancer survivors rarely use tools to report subjective data such as pain, fatigue, and distress [6]. Moreover, many patients face difficulties to receive sufficient and appropriate information applicable to their daily lives [7]. Thus, development of a comprehensive, easy-to-access platform for managing oncological outcomes, body composition, and functional status is becoming indispensable since their alterations may influence the prognosis of the disease [4].

Mobile health care application has emerged as an encouraging device in managing the clinical course of cancer and improving quality of life and physical performance in cancer survivors. Mobile health is defined as the provision of health services and information through mobile and wireless technologies [8]. A previous study showed that physical capacity including muscle strength of lower extremities and cardiorespiratory endurance and treatment-related symptoms, such as fatigue, nausea, and vomiting, were significantly improved in colorectal cancer patients through a tailored rehabilitation exercise program supported by mobile health applications [1]. However, generalization to overall colorectal cancer patients could not be done owing to a limited number of patients and confinement to a specific phase of the treatment.

To the best of our knowledge, randomized clinical trials that applied a personalized, phase-specific digital health program using mobile application and smart bands to a large number of patients with colorectal cancer have not yet been conducted, especially starting immediately post cancer operation. The primary objective of this protocol is to clarify the effect of mobile application and wearable smart band on skeletal muscle mass increment in patients with colorectal cancer. The secondary outcomes will be improvement in quality of life, enhanced physical fitness level, increased physical activity, diminished pain intensity, decreased severity of the low anterior resection syndrome, weight, and fat mass.

## Methods

### Study design

This protocol will be a prospective multi-centered two-armed randomized controlled trial. The study design meets SPIRIT guidelines [9]. The SPIRIT Checklist are attached as Additional file 1. Colorectal cancer patients will be recruited from three university hospitals in South Korea (Samsung Medical Center, Korea University Anam Hospital, and Seoul St. Mary’s Hospital). The enrolled participants will be randomly allocated to either the digital therapeutic or control group. Regardless of group allocation, all patients will receive conventional education and usual care in hospital. Patients who undergo colostomy will receive colostomy care by hospital staffs. Furthermore, patients who underwent low anterior resection surgery will receive education of the pelvic floor muscle rehabilitation by a physical therapist, 2–4 weeks after surgery. The flow diagram of the study protocol is shown in Fig. 1.

### Participants

In this study, we will enroll 324 participants who were diagnosed with colorectal cancer and have undergone surgery. The inclusion criteria will be as follows: (a) aged 19–85 years, (b) diagnosed with colorectal cancer and undergone colorectal cancer resection surgery, (c) uses an Android- or iOS-based smartphone, (d) able to use mobile application and have regular follow-up assessment as outpatient, (e) voluntary participation. The exclusion criteria will be as follows: (a) unable to perform exercise and diet management because of severe underlying disease, neuromusculoskeletal disease, or cognitive or visual impairment, (b) communication difficulties.

All eligible patients will be informed about this study, and after consultation with the department of surgery and the department of rehabilitation medicine they will be invited to participate. All patients will submit a written informed consent if they agree to participate in the study.

### Randomization, allocation, and blinding

We used blocked randomization with randomly selected block sizes (block size: 3 and 6). This study is an open study; therefore, the name of the group is not blinded. Owing to the nature of the intervention, the participant and evaluator can recognize which intervention has been assigned to the participant. After randomly allocating patients into two groups with a 1 (control group): 2 (intervention group) ratio, baseline assessment will be performed.

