### Outcome measures

Outcomes will be assessed at baseline and at 1-, 3-, 6-, and 12-month follow-ups. Outcome measures will be assessed by clinical research coordinator and summary of baseline screening, assessment, and follow-up during study visits is described in Table 2.

**Table 2 Tab2:** Summary of baseline screening, assessment, and follow-up during study visits

		STUDY PERIOD				
		Post-allocation				
TIMEPOINT		*Post op* *(± 1w)*	*1-month* *(± 2w)*	*3-month* *(± 1 m)*	*6-month* *(± 2 m)*	*12-month* *(± 2 m)*

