	**INTERVENTIONS**:					
	***Personalized digital therapeutic (intervention) group***					
	***Control group***					
	**ASSESSMENTS**:					
***7***	***Complication***		X	X	X	X
***8***	***Hb, albumin***	X ^1)^			X	X
***9***	***CT (visceral fat, muscle mass)***	X ^1)^			X	X
***10***	***Body composition***	X	X	X	X	X
***11***	***EORCT-QLQ-C30***	X	X	X	X	X
***12***	***EORCT-QLQ-CR29***	X	X	X	X	X
***13***	***MNA***	X	X	X	X	X
***14***	***IPAQ-SF***		X	X	X	X
***15***	***Grip strength***	X	X	X	X	X
***16***	***30 s chair stands test***		X	X	X	X
***17***	***2 min walk test***		X	X	X	X
***18***	^***a***^ ***LARS***		X	X	X	X
***19***	^***b***^ ***Satisfaction questionnaire***				X	

*CT*: computed tomography, *EORCT-QLQ*: European Organization for Research and Treatment of Cancer-Quality of life Questionnaire, *MNA*: Mini Nutritional Assessment, *IPAQ-SF*: International Physical Activity Questionnaire-Short Form, *LARS*: Low Anterior Resection Syndrome Score Questionnaire

^a^ Rectal cancer without ileostomy and colostomy.

^b^ Digital therapeutic group only.

^1)^ Tests analyzed within previous 6 months from the baseline can be collected.

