### Primary outcome

The primary objective of this study is to determine the effect of mobile application and wearable smart band in the management of prognostic factors in colorectal cancer patients. Therefore, the primary outcome would be the skeletal muscle mass increment in the intervention group compared to the control group in 12 months from the baseline, measured using the bio impedance analysis.

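### Baseline is assessed after open allocation, which exposes the self-reported and effort-dependent baselines directly and the bioimpedance reference value only indirectly

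*Protocol article*

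**What the plan says.** The section Randomization, allocation, and blinding gives the order: "After randomly allocating patients into two groups with a 1 (control group): 2 (intervention group) ratio, baseline assessment will be performed". It also says "This study is an open study; therefore, the name of the group is not blinded", and that "the participant and evaluator can recognize which intervention has been assigned to the participant". The abstract describes the design differently ("This study is a prospective, multi-center, single-blinded, two-armed, randomized controlled trial") but names no blinded party.

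Under Outcome measures, "Outcomes will be assessed at baseline and at 1-, 3-, 6-, and 12-month follow-ups". Table 2 schedules body composition, QLQ-C30, CR29, MNA and grip strength at the post-operative visit, which has a window of ±1 week. Only haemoglobin/albumin and CT may be taken from tests in the preceding 6 months. eHEALS is given at this visit to the digital group alone.

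The primary outcome is defined as "skeletal muscle mass increment in the intervention group compared to the control group in 12 months from the baseline, measured using the bio impedance analysis". The Statistical analysis section plans an independent t-test for it if the data are normal. It also plans tests of baseline differences, with a regression correction if randomisation turns out unbalanced.

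**The concern.** A baseline is useful because allocation cannot have affected it. That no longer holds once the arm is known before the measurement. A patient who has just learned the arm may answer a quality-of-life questionnaire differently or grip with different effort, and an evaluator who knows the arm may encourage or score differently. Someone who leaves between allocation and baseline has no reference value, and so no increment.

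Two parts of the analysis depend on this. An increment carries any arm-related shift in the reference value in full, with the sign reversed. And the plan to test and correct baseline differences presumes that they arise by chance. With a post-allocation baseline, a difference may be a consequence of allocation, and correcting for it is then not a neutral step.

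**Working it through.** **Order and knowledge of the arm.** The sentence on allocation and baseline is explicit. The open-study statement stands in the same section, and no passage describes a masked baseline assessor or a pre-allocation measurement of the items above. The eHEALS row points the same way: an item given to one arm only at the baseline visit requires the arm to be known at that visit. The Table 2 header "Post-allocation" is consistent with the order but is weak support, because it also spans screening and consent.

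**Which measures are exposed.**

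| Measure | Entry at post-op visit | Exposure |
|---|---|---|
| QLQ-C30, CR29, MNA | yes | direct (wholly or partly self-reported) |
| Grip strength | yes | direct (effort) |
| Bioimpedance ("Body composition") | yes | indirect |
| CT, haemoglobin/albumin | yes, may predate allocation | small |
| IPAQ-SF, LARS, chair stand, walk test | no | none at baseline |
| eHEALS | digital group only | no between-arm comparison |
| Pain NRS | no row in Table 2 | cannot be determined |

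**The plan's own sample size.** Inputs from Sample size calculation: effect size 0.35, power 80%, ratio 1:2. The 5% level is from Statistical analysis. Sidedness is not stated.

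- Two-sided: n(control) = (1 + 1/2) × (1.960 + 0.842)² / 0.35² = 1.5 × 7.85 / 0.1225 ≈ 96.1, so 97, with 2 × 97 = 194 in the intervention arm. The plan states 97 and 195.
- Noncentral-t power at 97 and 195 is 80.2%. One-sided testing would give 76 and 152, so two-sided is the match.
- Dropout of 10%: 97/0.9 = 107.8 and 195/0.9 = 216.7, against the stated 108 and 216.

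The sample size reproduces and is not in question.

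**Illustration of a baseline shift (assumption only).** Let b be a differential shift in the reference value, in SD of the 12-month change. Assume that follow-up values are unaffected, and read 0.35 as being on the same scale. The change-score difference moves by b. With 97 and 195, the noncentrality is b × √(97 × 195 / 292) = b × 8.05. Two-sided 5% t-test:

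| b | b / 0.35 | Rejection rate with no true effect | Power at 0.35 if the shift runs against the intervention |
|---|---|---|---|
| 0.05 | 14% | 6.9% | 67% |
| 0.10 | 29% | 12.6% | 52% |
| 0.15 | 43% | 22.5% | 36% |
| 0.20 | 57% | 36.1% | 23% |

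The table shows how sensitive the test is to a shift. It does not say how likely a shift of any size is.

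**The case against.** The strongest reply concerns the primary outcome. Skeletal muscle mass by bioimpedance is neither an opinion nor an effort score, and knowing the arm does not by itself move a device reading. This stands. A reader might infer that the primary result is biased by patients or staff knowing the arm. The documents do not support that; they leave open only the indirect routes of timing within ±1 week, measurement conditions, early use of the app and band, and withdrawal before baseline.

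A reader might also infer that every questionnaire is affected. IPAQ-SF and LARS have no baseline entry, so this does not hold.

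The attrition route is limited as well. Table 2 puts consent, allocation and baseline in one column. If they occur at one sitting, there is little time for arm-dependent withdrawal. The ±1 week window allows some gap, but no figure for differential loss can be drawn from the documents.

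The text says that the arm can be recognised, not that it always is, and recognition may be less certain before the app and band are in use. This softens the point without removing it: the study is declared open, and nothing provides for concealment until baseline is complete. The abstract's single-blind label does not help, since it conflicts with the methods section and names nobody as blinded.

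**Conclusion.** The concern holds in a limited form. The order of allocation then baseline is stated outright, in an open trial with no masked baseline assessor described. The direct risk is to QLQ-C30, CR29, MNA and grip strength, all secondary outcomes. The risk to the primary reference value is real but indirect.

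The size is unknown. The range of 14% to 57% of the planned effect, and false-positive rates of about 7% to 36%, rests entirely on an assumed shift of 0.05 to 0.20 SD of change. It should not be read as an estimate, least of all for bioimpedance. The change is worth making because it removes the question at almost no cost, not because bias has been shown.

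**What to change.** **Future participants.** At the same post-operative visit, obtain consent and complete all scheduled baseline measures: bioimpedance, QLQ-C30, CR29, MNA, grip strength, and pain NRS if it is taken at baseline. Only then release the allocation. eHEALS follows, since it is for the digital group alone. Reconcile the abstract's single-blind description with the open-study statement.

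**Participants already enrolled.** Trial status says that recruitment has begun. Report the order used, the allocation-to-baseline interval and the number lost before baseline, each by arm. Do not read baseline differences in these participants as chance imbalance to be corrected by regression. Excluding everyone assessed after allocation is not a useful sensitivity analysis, because under the stated order it would remove all participants enrolled before the change.

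**Cost.** No added patients, visits or measurements. The app and band are handed out slightly later at that visit, and two short by-arm summaries are added to the report.

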**Fig. 1 Fig1:**
[figure not shown]
Flow chart of the randomized controlled trial

### Interventions

#### Personalized digital therapeutic (intervention) group

For the personalized digital therapeutic group, Colon Cancer by Second Doctor program (Medi Plus Solution, Seoul, Korea) for health management after colorectal cancer surgery and DoFit as a smart band on the wrist (NF-B20, Medi Plus Solution, Seoul, South Korea) will be used. The application and fundamental contents are developed by an expert team consisting of app developers, designers, service programmers, cancer rehabilitation specialists, and researchers as the basis of evidence. It can be used on both Android and iOS platforms. Data collected from smart band can be transferred to application via Bluetooth connection. This smart band is capable of measuring the physical activity (step counts and energy expenditure), heart rate through a built-in 6-axis accelerometer, gyroscope, and photoplethysmography sensor. In addition, information from smart devices such as blood pressure monitors, blood glucose monitors, and weight scales can be linked with the application.

The key app functions are indicated in Table 1 and screenshots of representative functions are shown in Fig. 2. User information for the algorithms of personalized content includes treatment type (chemotherapy), hypertension, initial weight, age, perceived rating of exertion, and comorbid diseases. After the primary analysis using these factors, the user life log data is repeatedly analyzed to provide a tailored guide.

Health care professionals can monitor the individual usage of participant using a web-based open architecture management program including all life log data. To manage the adherence to the mHealth-based intervention, we will monitor the application usage rate every 2 weeks for 12 months, and feedback will be provided during initial 3 months.

### Control group

The control group will go through conventional education and usual care in hospital for 12 months.

**Table 1 Tab1:** Functions of the mobile application and key characteristics

Functions	Key characteristics
Expert consultation	• It provides expert consultations regarding exercise and nutrition using text messages, voice recordings, and images. It does not apply to consultations on symptoms. User can receive the result of consultation within 24 h.
Second doctor Journal	• It offers health information and education contents regarding exercise, nutrition, and disease according to the surgery, treatment type, and comorbidities.
Exercise management	• It offers an aerobic exercise program with target heart rate and exercise time according to the user’s treatment type. In addition, using a weekly step-by step approach, the exercise program with video clips is provided by combination of stretching and muscle strengthening exercises and pelvic floor muscle training. • The contents of exercise are personalized according to the user information (surgery and treatment type); difficulty is adjusted by rating the perceived exertion after the exercise.
Diet management	• If a user inputs their daily diet using speech recognition and text input functions, it provides feedback of the intake, food balance, and protein and fat, with the marking as insufficient, adequate, or excessive. • The weight information entered at the time of membership registration becomes the standard for the initial recommended calorie intake. • It simply recommends foods and its amount for breakfast, lunch, dinner, and snacks. Moreover, it recommends nutritional intake according to comorbid diseases from the 13th week.
Physical activity management	• It recommends the target stepping intensity, burning of calories, and heart rate (e.g., 5,000 steps, 200 kcal, etc.). The number of steps according to the step type is displayed.
Comorbidity and Weight management	• It indicates target blood pressure and blood glucose level based on the clinical practice guidelines. • It informs the user whether their weight is within the normal weight range.

**Fig. 2 Fig2:**
[figure not shown]
Screenshots of the representative function and smart-band: (A) home (today’s to do list), (B) second doctor journal, (C) exercise management, (D) weight management, (E) diet management, (F) exercise video (pelvic floor muscle training), and (G) DoFit. Reproduced with permission of Medi Plus Solution. Co., Ltd

### Outcome measures

Outcomes will be assessed at baseline and at 1-, 3-, 6-, and 12-month follow-ups. Outcome measures will be assessed by clinical research coordinator and summary of baseline screening, assessment, and follow-up during study visits is described in Table 2.

**Table 2 Tab2:** Summary of baseline screening, assessment, and follow-up during study visits

		STUDY PERIOD				
		Post-allocation				
TIMEPOINT		*Post op* *(± 1w)*	*1-month* *(± 2w)*	*3-month* *(± 1 m)*	*6-month* *(± 2 m)*	*12-month* *(± 2 m)*
	**ENROLLMENT**:					
***1***	***Eligibility screening***	X				
***2***	***Informed consent***	X				
	***Allocation***	X				
***3***	***Demographic characteristic***	X				
***4***	***Medical history***	X				
***5***	***Health lifestyle***	X				
***6***	^***b***^ ***eHealth Literacy Scale***	X				
